#### Sample size calculation

The rate of the expectation of efficacy in the Tuina group is 95% and in the health care education group is 85%, based on the literature. The sample size was calculated with a significance level of 0.05 and power of 0.80, which also considers a maximum dropout tolerance of 10%. Ultimately, 160 patients are needed for the trial, with 80 for each group.

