**Methods/design:**

This study is a randomized controlled trial with parallel-group design including two groups: a Tuina group and a health care education group. A total of 160 eligible participants will be randomly assigned to the groups in a 1:1 ratio. The interventions of both groups will last for 20 min and be carried out twice each week for a period of 12 weeks. The primary outcome is the Oswestry Disability Index. The secondary outcomes include a visual analogue scale and the 36-item Short Form Health Survey. They will be assessed at baseline, at the end of the intervention every month, and during 6 months and 9 months of follow-up by repeated measures analysis of variance. The significance level is 5%. The safety of Tuina and health care education will be evaluated after each treatment session. This study will focus on the value of Tuina and health care education for low back pain and will highlight any differences in the efficacy of the treatments.

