### Primary outcome measurement

#### Oswestry Disability Index

The primary outcome is the subject’s perceived disability, which is assessed by the modified Oswestry Disability Index (ODI) [36]. The ODI consists of ten items, including pain intensity, personal care, lifting, walking, sitting, standing, sleep, sex life, social life, and traveling. According to the extent of disability, each item is scored from 0 to 5. The total score is reported as a percentage, which is actual score/50 (maximum possible score) × 100%. The ODI results will be assessed using a repeated longitudinal analysis.

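### The sample size and its 80% power rest on an undefined binary efficacy rate, not on the ODI score that is the primary outcome

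*Protocol article*

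**What the plan says.** The sample size section of the Protocol article gives the basis as "The rate of the expectation of efficacy in the Tuina group is 95% and in the health care education group is 85" per cent, attributed to the literature. It continues: "The sample size was calculated with a significance level of 0.05 and power of 0.80", "which also considers a maximum dropout tolerance of 10" per cent. The result is 160 patients, 80 per group.

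The abstract states: "The primary outcome is the Oswestry Disability Index". The ODI section defines it as the sum of ten items, each scored 0 to 5, expressed as a percentage of the maximum of 50. On its analysis it says: "The ODI results will be assessed using a repeated longitudinal analysis".

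The outcome section lists three questionnaires (ODI, VAS, SF-36) at six time points: baseline and months 1, 2, 3, 6 and 9. No section sets a threshold that turns any of them into a success or failure. The statistical section plans repeated measures ANOVA, rank-based tests or a linear mixed model, depending on checks of homogeneity and normality. Its chi-square and Fisher tests are for adverse events.

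**The concern.** A power statement belongs to one outcome, one effect and one test. Here the outcome is an efficacy rate that the article never defines, the effect is 95% against 85%, and the implied test compares two proportions. The trial's primary question concerns a mean difference in a score, and for that the article gives no target difference, SD, correlation or power.

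The percentages cannot be read as ODI scores. A higher ODI percentage means more disability, so 95% and 85% would describe near-total disability, worse under Tuina.

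What is at stake is the reason for enrolling 160 patients. A reader who sees 80% power next to a primary ODI outcome will take it as the chance of detecting a worthwhile ODI difference. Nothing in the article supports that.

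**Working it through.** **Inputs from the article.** Rates 0.95 and 0.85; alpha 0.05, sidedness not stated; power 0.80; dropout 10%; 80 per arm, allocation 1:1. Evaluable per arm after dropout: 80 × 0.90 = 72.

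**Step 1: try to reproduce 80 per arm from the stated rates.** Two-sided, pooled variance under the null, with mean rate 0.90:

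n = [1.960 × √(2 × 0.90 × 0.10) + 0.842 × √(0.95 × 0.05 + 0.85 × 0.15)]² / 0.10²
= (0.8315 + 0.3521)² / 0.01 = 140.1, so 141 per arm.

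With dropout: 141 / 0.90 = 156.7, so 157 per arm, 314 in total.

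Other versions of the calculation:

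| Method | Per arm | Per arm after 10% dropout |
|---|---|---|
| Two-sided, pooled | 141 | 157 |
| Two-sided, continuity-corrected | 160 | 178 |
| Two-sided, unpooled | 138 | 154 |
| Two-sided, arcsine | 133 | 148 |
| One-sided, pooled | 111 | 124 |
| One-sided, arcsine | 105 | 117 |

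None gives 80 per arm.

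**Step 2: power of the stated size for the stated rates.** Two-sided:

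power = Φ[(0.10 × √n − 0.8315) / √0.175]

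- n = 72: Φ[(0.8485 − 0.8315) / 0.4183] = Φ(0.041) = 52%.
- n = 80: Φ[(0.8944 − 0.8315) / 0.4183] = Φ(0.150) = 56%.

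One-sided power is 64% and 68%. Fisher's exact test, two-sided, gives 42% and 48%.

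**Step 3: what the fixed size can detect on the ODI.** The article gives no ODI SD or correlation, so this step is illustrative. It takes a two-sample comparison of means at one time point, two-sided 5%, 80% power. It does not model the planned repeated-measures analysis.

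- Normal approximation, 72 per arm: (1.960 + 0.842) × √(2/72) = 0.467 SD. Solved with the noncentral t: 0.470 SD.
- With 80 per arm (no dropout), normal approximation: 2.802 × √(2/80) = 0.44 SD.
- Adjusted for baseline, multiply by √(1 − r²). With an assumed r = 0.5: 0.470 × 0.866 = 0.41 SD. With an assumed r = 0.7: 0.470 × 0.714 = 0.34 SD.

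In ODI points, 72 per arm, SD assumed:

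| Assumed SD | Unadjusted | r = 0.5 | r = 0.7 |
|---|---|---|---|
| 10 | 4.7 | 4.1 | 3.4 |
| 15 | 7.1 | 6.1 | 5.0 |
| 20 | 9.4 | 8.1 | 6.7 |

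For an assumed true difference of 5 points, unadjusted power with 72 per arm is about 85%, 51% or 32% at SD 10, 15 or 20. For 10 points it is over 99%, 98% or 85%. The same 160 patients can be ample or too few, depending on figures the article does not state.

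**The case against.** The mismatch itself is plain in the text. The case on the other side concerns how far it reaches, and much of that stands.

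- **A reader might infer that the trial is underpowered for the ODI.** The article does not support this. Step 3 shows that 160 may or may not be enough.
- **A reader might infer that a null ODI result could not be interpreted.** It could. The statistical section promises 95% confidence intervals, and a null result is read from the interval, not from a planning figure.
- **A reader might say the rate comparison will never be run.** That is too strong. A full protocol or analysis plan, not shown, could define an efficacy rate. What can be said is that this document defines no such outcome and plans no such test.
- **A reader might carry the 52% over to a responder rate derived from the ODI.** It belongs only to the undefined 95% and 85%. Nothing suggests an ODI-based responder would have those rates.
- **The ODI figures are simplified.** They use one time point, while the plan is longitudinal. Baseline adjustment appears in only one conditional branch of the plan, the linear mixed model used when initial homogeneity is not found. The correlations and SDs are assumptions, and the 72 counts completers although the primary analysis follows intention to treat.

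The condensed format does not excuse the core point. The article states a basis for its sample size, and that stated basis does not match its stated primary outcome.

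**Conclusion.** The concern holds as a defect of justification. The 80% power is attached to an undefined binary rate, so it does not apply to the primary ODI comparison, and 160 is not justified for the ODI by anything in this document. The claim also fails on its own terms: two-sided power for 95% against 85% is about 52% at 72 per arm and 56% at 80, and no method tried gives 80 per arm.

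The two-sided per-arm figure after dropout (157) is close to the stated total of 160, so a per-arm number may have been taken as the total. The article does not say so, and the verdict does not depend on it.

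The 52% and 56% rest on the article's own inputs and a two-sided test. The detectable ODI differences rest on assumed SDs and correlations and show only the range of possible answers.

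**What to change.** Amend the sample size section as follows.

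1. Keep 160, and reconcile it with the legend of Fig. 1, which gives 180 randomised.
2. Keep the rate-based calculation on record as the basis on which 160 was chosen, but withdraw the 80% claim for it. State that those rates give about 52% power two-sided with 72 evaluable per arm, and about 56% with 80.
3. Add the detectable between-arm ODI difference at a named primary time point, two-sided 5%, 80% power, 10% dropout, with a sourced ODI SD and baseline correlation. Month 3 is one possible choice; the article names none. Label this as calculated after the size was fixed, because recruitment is already under way.
4. If an ODI responder rate is wanted, define it, list it as secondary and compute its power from rates sourced for that definition.

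The cost is a reworded paragraph and a search for the SD and correlation; no patients or data are added. The downside is that the stated power becomes less favourable.

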#### Statistical analyses

The intention-to-treat principle will be followed in the primary data analysis with IBM SPSS Statistics for Windows version 21.0 software by statisticians who are blinded to the group allocation. The baseline characteristics will be expressed with descriptive statistics for the two groups, which are reported as the mean ± standard deviation. A Kolmogorov-Smirnov test with Lilliefors correction will be used to analyze all quantitative variables to determine whether they follow a normal distribution. Parametric statistics (Tukey test) or nonparametric statistics (Wilcoxon rank-sum test) will be used for the within- and between-group analyses in accordance with the results of the homogeneity and normality analyses. When initial homogeneity and normality of data distribution are found, repeated measures analysis of variance (ANOVA) and ANOVA with Bonferroni *post hoc* statistics will be used to analyze within and between groups. The Friedman test and Kruskal-Wallis test will be used when initial homogeneity but not normality of data distribution is found. If the initial homogeneity is not found, a linear mixed model will be adjusted for the baseline value. Adverse events in each group will be documented as percentage for safety assessments using the chi-square test or Fisher’s exact test. The statistical significance is defined as *P* < 0.05, and the 95% confidence interval will be reported.

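### The sample size does not follow from its stated inputs: 95% versus 85% at 80% power needs about 157 per arm, and 80 per arm gives about 52% power

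*Protocol article*

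**What the plan says.** The protocol article, under "Sample size calculation", gives all the main inputs and the result:

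- Effect: "The rate of the expectation of efficacy in the Tuina group is 95% and in the health care education group is 85" per cent.
- Error rates: "The sample size was calculated with a significance level of 0.05 and power of 0.80".
- Attrition: "which also considers a maximum dropout tolerance of 10" per cent.
- Result: "Ultimately, 160 patients are needed for the trial, with 80 for each group".

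The abstract repeats the size and gives the allocation: "A total of 160 eligible participants will be randomly assigned to the groups in a 1:1 ratio". The sections on study design and randomization carry the same numbers. The Fig. 1 caption instead gives 180 as the number to be randomised.

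The paragraph states neither the sidedness of the test nor the formula. The statistical analyses section sets significance at P < 0.05 and adds that "the 95% confidence interval will be reported", which points to a two-sided test.

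**The concern.** A 10-point difference between two high response rates usually needs well over 100 patients per arm for 80% power, so 80 per arm with dropout already included looks too small.

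This paragraph is the article's only justification for the trial's size. If it is wrong, readers and the ethics committee have been told of a power that the protocol's own assumptions do not deliver. A test of the assumed difference would miss it about half the time if it were real, and a null result could then be misread as evidence that the two treatments do not differ.

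**Working it through.** **Inputs.** From the sample size paragraph: p1 = 0.95, p2 = 0.85, difference 0.10, alpha 0.05, power 0.80, dropout 10%, 80 per arm. From the abstract: 1:1 allocation. Assumption: two-sided test, so z = 1.96 for alpha and 0.8416 for power. The average rate is 0.90. The pooled variance term is 2 × 0.9 × 0.1 = 0.18. The unpooled term is 0.95 × 0.05 + 0.85 × 0.15 = 0.175.

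**Attempt to reproduce 80 per arm.** The standard formula gives

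n = [1.96 × √0.18 + 0.8416 × √0.175]² / 0.10² = 140.1, so 141 evaluable per arm.

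Allowing for dropout, 141 / 0.9 = 156.7, so 157 per arm and 314 in total.

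The stated 80 per arm leaves 80 × 0.9 = 72 evaluable. No usual two-sample variant comes down to 72, or even to 80:

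| Method | Evaluable per arm | Per arm after 10% dropout |
|---|---|---|
| Two-sided, pooled | 141 | 157 |
| Two-sided, unpooled | 138 | 154 |
| Two-sided, arcsine | 133 | 148 |
| Two-sided, continuity-corrected | 160 | 178 |
| One-sided, pooled | 111 | 124 |
| One-sided, arcsine (smallest) | 105 | 117 |
| One-sided, continuity-corrected | 130 | 145 |

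**Power at the stated size.** Two-sided, by normal approximation:

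Power = Φ[(0.10 × √n − 1.96 × √0.18) / √0.175]

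- n = 72: (0.8485 − 0.8315) / 0.4183 = 0.041, so power is 51.6%.
- n = 80: (0.8944 − 0.8315) / 0.4183 = 0.150, so power is 56.0%.

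Exact enumeration and the one-sided approximation compare as follows:

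| Test | 72 per arm | 80 per arm |
|---|---|---|
| Two-sided, normal approximation | 51.6% | 56.0% |
| Two-sided chi-square, exact | 53.6% | 57.3% |
| Two-sided Fisher's exact test | 42.2% | 48.1% |
| One-sided, normal approximation | 64.1% | 68.1% |

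**What 72 per arm can detect.** With 95% in the Tuina arm, 80% power needs an education rate of about 79.6%. That is a difference of about 15 points, not 10.

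**Possible source of the error.** Two routes lead close to the stated numbers. The two-sided requirement per arm (157) is near the stated total (160). Leaving the factor of 2 out of the average-rate formula gives 7.849 × 0.09 / 0.01 = 70.6, and 70.6 / 0.9 = 78.5, or 79 per arm. Both are consistent with a per-arm figure having been used as the total. The article does not show its formula, so this remains an inference.

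**The case against.** **Sidedness and dropout are assumptions.** The article states no sidedness, and 10% is described as the most dropout tolerated, not what is expected. With all 160 patients analysed, two-sided power is 56%, not 52%. This stands as a condition on the 52%, but every combination in the working remains well below 80%.

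**The trial does not test this endpoint.** This is the strongest objection. The primary outcome is the ODI percentage score, analysed longitudinally, and the article defines no responder rate. The 52% is therefore the power of a comparison that is not the primary analysis. The article gives no ODI difference or standard deviation, so power for the ODI could lie above or below 80%. This limits the conclusion: the stated justification is wrong, but the trial has not been shown to be underpowered for the ODI. It does not rescue the paragraph, which fails on its own terms.

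**Another formula comes close to 80.** A one-sample test against a fixed 85% gives 78.0, so 79. That does not fit a comparison of two randomised arms, and it leaves no room for the dropout that the paragraph says was included. It does show that closeness to 80 or 160 cannot identify the mistake, so the cause stays uncertain.

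**The Fig. 1 caption gives 180.** At 90 per arm with no dropout, two-sided power is about 61%; with 81 evaluable per arm it is about 56%. The larger number does not help either.

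**Conclusion.** The concern holds. From the stated inputs, the required size is about 157 per arm (314 in total), roughly twice the stated 80 per arm (160). At the stated size, power for 95% versus 85% is about 52% after 10% dropout and about 56% with none, against a claimed 80%.

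These headline figures assume a two-sided 5% test and the pooled normal approximation. The choice of test, sidedness or dropout handling moves power within about 42% to 68% and never to 80%. The figures describe the binary efficacy rate only. How the error arose is not established and does not affect the result.

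**What to change.** Correct the sample size paragraph without adding patients.

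- **Preferred:** replace the calculation with the power of 160 randomised patients (about 144 evaluable) for the ODI analysis, stating the assumed ODI difference, its standard deviation and the sidedness. These inputs must come from the sponsor, because the article does not give them.
- **Minimum:** keep the binary calculation but state that 160 randomised patients, about 144 evaluable, give about 52% power for 95% versus 85% at two-sided 5%, and that 80% power would have needed about 314.

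In either case, reconcile the 180 in the Fig. 1 caption with the 160 used elsewhere. Report the correction to the steering and ethics committees, as the quality control section provides for protocol changes.

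The minimum version costs the rewording of one paragraph and a less favourable stated power. The preferred version also needs sourced ODI assumptions. Neither changes treatment or data collection.

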#### Quality control

With the management of the steering committee, quality control will be conducted during the processing of the trial. Professional trial method and regular monitoring technique should be trained before the researchers participate in the trial, which can ensure the consistency of methods. The steering committee and ethics committee should be informed if the study protocol is modified or corrected.

## Discussion

A survey showed that low back pain has a high prevalence rate across the lifespan, which seriously affects quality of life. In addition, the medical cost is a leading contributor to disease burden wordwide [4, 38, 39]. Systematic reviews of risk factors for low back pain have suggested that the rising risk of back pain episodes is related to both physical and psychological risk factors [40]. It can be caused by prolonged standing and lifting heavy weights, an unhealthy lifestyle such as smoking and obesity, experiencing distress, and the expectations that pain indicates bodily harm or injury. So, targeted health education in primary care is necessary and has been shown to provide long-term reassurance for patients with low back pain [23].

Tuina therapy belongs to the key noninvasive therapies of traditional Chinese medicine, which is based on the theory of meridians and acupoints and modern anatomy. It takes advantage of the hands of the therapist to manipulate the surface of the patient, including relaxation techniques, such as pressing, kneading, and pushing, and some adjustment manipulations, such as pulling and shaking. The Huangdi Inner Classic Pain Theory states that “when your body feels pain, it means the balance in your body is disrupted.” Conversely, you will not feel any discomfort when your body’s qi is flowing smoothly through the meridians. Blood stagnation is caused by the stagnation of qi, which can lead to phlegm pattern as the process of the disease. The most obvious manifestation is characterized by stabbing pain in a fixed location, usually aggravated at night. Tuina can help the patient achieve a physiological balance of “blood and qi” by manipulation of “restrict bone and harmonize joints.” It has been found that patients with low back pain have a symptom that the muscle tension increases with local inflammatory stimulation and even continues to sputum in some biomechanical studies. Tuina is used to loosen muscle adhesions and significantly improves muscle strength of patients with low back pain. It can relieve the pathological fatigue state of the muscles, harmonize the coordinated balance function of the flexors and extensors, and finally restore a physiological balance of muscles and bones [41]. In previous studies, a rat model was established to demonstrate that Tuina could reduce pain sensitivity and peripheral nociceptive peripheral C-fiber activity in rats and could accelerate the repair peripheral nerve injury [42, 43].

However, the efficacy and safety of Tuina therapy requires further clinical proof. This trial is designed as a clinical randomized controlled trial to compare the efficacy of Tuina and health care education in patients with low back pain. The ODI, VAS, and SF-36 are being used as the outcome measurements, which can evaluate the efficacy of relieving pain and improve the quality of life with the interventions. This protocol intends to provide a more powerful evidence-based proof for Tuina therapy in patients with low back pain.

### Study limitations

There is an inevitable limitation that it is difficult to control the methodology of blinding during the physical intervention. In this study, Tuina and health care education are different forms of physical therapy, which cannot be blinded for the participants and therapists. Therefore, the blinding quality should be monitored to control the questionnaire measurement credibility, which is composed of the assessors, the administrators, and the data analysts.

## Trial status

This trial is still in the process of recruiting process. Participant recruitment started in June 2019 and will end in June 2020. This trial was registered in Chinese Clinical Trial Registry on 23 April 2019. The registration number is ChiCTR1900022656.

## Abbreviations

ANOVA: Analysis of variance
CRF: Case report form
ICD­11: International Classification of Diseases, 11th Revision
ODI: Oswestry Disability Index
SF-36: 36-Item Short Form Health Survey
VAS: Visual analogue scale
